## Abstract

**Background:**

Chronic work-related stress is a significant and independent risk factor for cardiovascular and metabolic diseases and associated mortality, particularly when compounded by a sedentary work environment. Heart rate variability (HRV) provides an estimate of parasympathetic and sympathetic autonomic control, and can serve as a marker of physiological stress. Hatha yoga is a physically demanding practice that can help to reduce stress; however, time constraints incurred by work and family life may limit participation. The purpose of the present study is to determine if a 10-week, worksite-based yoga program delivered during lunch hour can improve resting HRV and related physical and psychological parameters in sedentary office workers.

**Methods and design:**

This is a parallel-arm RCT that will compare the outcomes of participants assigned to the experimental treatment group (yoga) to those assigned to a no-treatment control group. Participants randomized to the experimental condition will engage in a 10-week yoga program delivered at their place of work. The yoga sessions will be group-based, prescribed three times per week during lunch hour, and will be led by an experienced yoga instructor. The program will involve teaching beginner students safely and progressively over 10 weeks a yoga sequence that incorporates *asanas *(poses and postures), *vinyasa *(exercises), *pranayama *(breathing control) and meditation. The primary outcome of this study is the high frequency (HF) spectral power component of HRV (measured in absolute units; i.e. ms^2^), a measure of parasympathetic autonomic control. Secondary outcomes include additional frequency and time domains of HRV, and measures of physical functioning and psychological health status. Measures will be collected prior to and following the intervention period, and at 6 months follow-up to determine the effect of intervention withdrawal.

**Discussion:**

This study will determine the effect of worksite-based yoga practice on HRV and physical and psychological health status. The findings may assist in implementing practical interventions, such as yoga, into the workplace to mitigate stress, enhance health status and reduce the risk of cardiovascular and metabolic diseases.

**Trial Registration:**

ACTRN12611000536965

URL: http://www.anzctr.org.au/ACTRN12611000536965.aspx

## Background

Epidemiological studies have consistently demonstrated that chronic work-related stress is a significant and independent risk factor for cardiovascular and metabolic diseases and associated mortality [1-4]. For example, a study enrolling over ten thousand participants concluded that individuals with high work-related stress were more than twice as likely to develop metabolic syndrome versus those reporting lower levels of stress [1]. Studies have also noted a strong association between work-related stress and coronary artery disease (CAD) [3,4] and a recent meta-analysis has concluded that work stress can increase the risk of myocardial infarction by 50% [2].

The link between stress and chronic disease is mediated by endocrine pathways of the sympathetic nervous system (SNS) including the hypothalamus-pituatary-adrenal (HPA) axis [5,6]. Cortisol, the main effector of HPA activation, increases circulating fatty acid and glucose concentrations and inhibits insulin. This hormone-mediated pathway prepares the body for physical exertion (i.e. "fight or flight"). The actions of cortisol are particularly concerning in a sedentary work environment given that psychological stress compounded by inactivity induces hyperlipidemia and hyperglycemia, antecedents to more advanced cardiometabolic disease (e.g. hypertension, obesity, type 2 diabetes, CAD, etc.) [7-9]. Interventions that holistically mitigate work-related stress and inactivity may reduce the risk of chronic diseases.

Yoga is an ancient system of practices based on the scientific principles of exercise, breathing and meditation, and philosophical beliefs concerning life and thinking [10]. The origin of yoga has been ascribed to the Indus Valley Civilization (2600-1900 BCE) although some researchers suggest more ancient origins [11,12]. Participation in yoga has increased dramatically throughout the world in recent decades [13]. Many styles of yoga have been tested in the clinical setting and most involve the performance of physical postures (*asanas*), breathing exercises (*pranayama*) and meditation [10]. Randomized controlled trials published in leading medical journals have revealed that yoga can induce significant and broad-ranging health adaptations, both in apparently healthy and chronically diseased cohorts [14-18].

Heart rate variability (HRV) is the beat-to-beat variation in heart rhythm due to autonomic influence on the sinoatrial node. Higher HRV indicates greater parasympathetic control while lower HRV indicates lesser parasympathetic control. Low HRV is an established predictor of cardiovascular morbidity and mortality [19]. Notably, studies have shown that excess job strain reduces HRV [20]. By contrast, two recent trials analysing HRV have demonstrated that participation in yoga sessions can acutely increase HRV [21,22]; however, there are currently no data to suggest that these effects can be maintained long term. An increase in resting HRV secondary to prolonged yoga training would indicate lower physiological stress and reduced risk of chronic diseases and early mortality.

It is oftentimes difficult for individuals to commit to stress-reducing practices due to the time restrictions incurred by work and family life. We postulate that integrating yoga into the workplace could provide a time-effective, convenient and practical method of abating the damaging effects of stress and inactivity. Yoga requires minimal space and minimal investment in equipment, and the potential benefits to health status, wellbeing, job satisfaction and work-related productivity could be significant.

Only two trials have evaluated the effect of a worksite-based yoga program on health-related outcome measures [23,24]. However, neither study evaluated changes in HRV. Therefore, the primary purpose of the present study is to determine the effect of a worksite-based yoga program on resting HRV and associated parameters in a cohort of office workers. We hypothesize that a worksite based yoga program will increase HRV, reflective of greater parasympathetic (vagal) tone, and that this adaptation will be accompanied by improvements in physical fitness and psychological health status, including quality of life, anxiety, and job satisfaction.

## Methods and design

### Study Design

This is a parallel-arm randomized controlled trial that will compare the outcomes of participants assigned to the experimental treatment group (yoga) with those assigned to a no-treatment control group. The primary outcome of this study is the high frequency (HF) spectral power component of HRV (measured in absolute units; i.e. ms^2^), a measure of parasympathetic autonomic control. Secondary outcomes include additional frequency and time domains of HRV, and measures of physical functioning and psychological health status. The intervention period will be 10 weeks, and the assessment of primary and secondary outcome measures will be completed prior to and following the intervention period and at 6 months follow-up to determine the effect of intervention withdrawal. The University of Western Sydney Human Research Ethics committee has approved all research procedures.

### Sample Size and Power Calculation

To our knowledge there are no published data on the effects of yoga training on resting HRV in a non-clinical population. However, it has been shown that yoga induces adaptations that are similar to those achieved with conventional exercise [25]. Therefore, data derived from an aerobic exercise intervention trial in an apparently healthy adult cohort [26] has been used to compute statistical power *a priori *using the non-commercial statistical power analysis program G*Power. The control group is expected to experience no change in the HF spectral power component from baseline (205.7 ± 205.7 ms^2^) while an experimental group is expected to increase this measure following the 10-week yoga intervention (568.0 ± 696.0 ms^2^). Setting an alpha level of 0.05, approximately 56 participants (28 per group) will provide 80% power to detect a statistically significant difference between groups. Recruitment will be inflated to 67 participants to enable a 20% participant attrition rate.

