### Statistical Analyses

Primary analysis will be via intention-to-treat with all patients included regardless of dropout or level of adherence. Missing data will be imputed according to the maximum likelihood expectation algorithm *via *the Statistical Package for the Social Sciences (IBM©, SPSS Version 19.0). Data will be presented as the mean ± standard deviation or median and range, as appropriate. Confidence intervals will be used to express group differences. Changes between groups will be determined by analysis of covariance of the post-treatment score controlling for the baseline score. Effect sizes and 95% confidence intervals will be calculated. A p value of < 0.05 will be considered indicative of statistical significance; clinical significance will be interpreted in light of the meaningfulness and magnitude of the adaptations observed.

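### The stated 80% power with 28 per group does not follow from the printed means and SDs, which give about 74% two-sided

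*Protocol article*

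**What the plan says.** The protocol article, section Sample Size and Power Calculation, bases the calculation on an aerobic exercise trial in apparently healthy adults and names G*Power as the software. The control group is assumed not to change "from baseline (205.7 ± 205.7 ms^2"), and the yoga group is assumed to rise "following the 10-week yoga intervention (568.0 ± 696.0 ms^2"). The error rate is given by "Setting an alpha level of 0.05". The result is that "approximately 56 participants (28 per group) will provide 80% power to detect a statistically significant difference between groups". The section names no test, no sidedness and no correlation between baseline and follow-up.

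The Statistical Analyses section plans an analysis of covariance of the post-treatment score adjusted for baseline. It adds: "Effect sizes and 95% confidence intervals will be calculated. A p value of < 0.05 will be considered indicative of statistical significance".

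**The concern.** The paragraph prints everything that a simple two-group calculation needs, so its result can be checked, and the standard calculation does not return 28 per group at 80%. The control mean and SD are also printed as the same number, which raises the possibility of a transcription error in one of them.

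This is the article's only power statement, and it concerns the primary outcome, HF power in ms². Readers will rely on it if the result is null. On the plain two-sided reading of the printed inputs, the type II risk is about 26%, not 20%.

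**Working it through.** **Inputs** (Sample Size and Power Calculation): control 205.7, SD 205.7; yoga 568.0, SD 696.0; alpha 0.05; 28 per group, equal allocation; claimed power 80%. Sidedness is not stated. I take two-sided as the main reading because the Statistical Analyses section pairs 95% confidence intervals with p < 0.05, and I show one-sided beside it.

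**Step 1: standardised difference.**
- Difference = 568.0 − 205.7 = 362.3
- Pooled SD = √((205.7² + 696.0²)/2) = 513.2
- d = 362.3/513.2 = 0.706

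**Step 2: try to reproduce the plan's figure.** Two-sample t-test, noncentral t with 2n − 2 degrees of freedom and noncentrality d√(n/2). At n = 28 the noncentrality is 0.706 × √14 = 2.64.

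| Test | Power at 28 per group | n per group for 80% |
|---|---|---|
| t-test, two-sided | 73.7% | 33 (32 gives 79.4%, 33 gives 80.6%) |
| t-test, one-sided | 83.2% | 26 |
| Welch, two-sided | 72.6% | 34 |
| Welch, one-sided | 82.6% | 27 |
| Mann-Whitney (relative efficiency 0.955), two-sided | 71.7% | 35 |
| Mann-Whitney (relative efficiency 0.955), one-sided | 81.7% | 27 |
| t-test, simple average of the two SDs, two-sided | 84.0% | 26 |
| t-test, SD 696.0 in both arms, two-sided | 48.1% | 59 |

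No row returns 28. A two-sided t-test with 28 per group needs d of about 0.762 for 80% power, against 0.706 from the printed figures.

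**Step 3: could the repeated 205.7 explain the gap?** Change one number at a time, two-sided t-test.
- SD wrong, mean right: the most favourable case is a control SD of zero. The pooled SD is then 696.0/√2 = 492.1, d = 362.3/492.1 = 0.736, power at 28 per group is 77.2%, and 30 per group are needed. A smaller SD alone cannot restore 80%.
- Mean wrong, SD right: a control mean of 175 gives d = (568.0 − 175)/513.2 = 0.766, power 80.3% and exactly 28 per group. A mean of 170 gives d = 0.776, power 81.3% and again 28. An error in the mean could therefore explain the stated figure completely.

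**Step 4: the planned ANCOVA.** With baseline-to-follow-up correlation r, the noncentrality of the F test is N(d/2)²/(1 − r²), with 1 and N − 3 degrees of freedom and N = 56. The article gives no r, so these values are assumptions:

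| r | Power at 28 per group, two-sided |
|---|---|
| 0 | 73.7% |
| 0.30 | 77.6% |
| 0.35 | 79.1% |
| 0.38 | 80.1% |
| 0.40 | 80.8% |
| 0.50 | 85.0% |
| 0.60 | 90.0% |

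**The case against.** The strongest reply is that the shortfall comes from a test that the protocol neither names nor plans. The planned analysis is ANCOVA, and a modest correlation of about 0.38 is enough for 80% with 28 per group. Sidedness is also only inferred: the Background states a directional hypothesis, and a one-sided t-test has 83.2% power at 28 per group. One-sided Welch and Mann-Whitney calculations, at 27 per group, come close to the stated number. Finally, the gap is about six percentage points, and the text says approximately.

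Much of this stands. It rules out the stronger reading that a reader might infer, namely that the trial lacks 80% power for its primary analysis. The article does not give the correlation that would decide this, and the source trial is not available here. A reader might also infer that correcting the repeated 205.7 could not rescue the figure. That is true only if the SD is the wrong number; if the mean is wrong, the power calculation may be correct and only an input misprinted.

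What does not stand is that the paragraph is adequate as printed. No one-sided test is stated, and 95% intervals with p < 0.05 follow the two-sided convention. No correlation is stated, so ANCOVA cannot be the derivation that a reader reconstructs. The word approximately hardly covers the difference between 56 and 66 participants.

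**Conclusion.** The concern holds as a mismatch between stated inputs and stated result. From the printed means, SDs and alpha, a two-sided two-sample t-test has about 74% power with 28 per group, and 80% needs 33 per group (66 in total, not 56). The one-sided version needs 26 per group, so the printed 28 matches neither.

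The 74% rests on three assumptions: a two-sided test, an unadjusted comparison on the ms² scale, and both 205.7 values being correct. Relaxing any one of them can bring the power at 28 per group to 80% or more, so the documents do not show that the trial is underpowered. They show that the 80% cannot be derived from what is stated. This should be fixed, but it does not threaten the design.

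**What to change.** First, check both the control mean and the control SD of 205.7 against the source trial and correct whichever is wrong. Then do one of the following in Sample Size and Power Calculation:

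- Restate the result for the simple comparison. If both values prove correct, this reads: two-sided alpha 0.05; 56 completers give about 74% power by a two-sample comparison.
- Redo the calculation for the planned ANCOVA on the ms² scale, stating the test, the sidedness and the assumed baseline-to-follow-up correlation with its justification.

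No extra participants are needed, and the primary outcome and analysis stay as they are. The cost is one reworded paragraph and possibly a slightly less favourable stated power.

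### Recruiting 67 allows for about 16% attrition, not 20%: a 20% loss leaves 53 to 54 participants, below the 56 the plan needs

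*Protocol article*

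**What the plan says.** Under Sample Size and Power Calculation, the protocol article states that "approximately 56 participants (28 per group) will provide 80% power to detect a statistically significant difference between groups". It then moves from that requirement to the recruitment target: "Recruitment will be inflated to 67 participants to enable a 20% participant attrition rate". The section gives no other attrition rate and no other basis for 67. The Statistical Analyses section plans an intention-to-treat analysis and adds that "Missing data will be imputed according to the maximum likelihood expectation algorithm".

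**The concern.** The recruitment target exists to protect the number of participants with outcome data. A reader takes from it that one in five can drop out and the required 56 will still be there. If 67 was reached by adding 20% to the required number, rather than by allowing for a 20% loss among those recruited, that reading is wrong. The error also overstates the protection. At stake are the accuracy of a published design statement and a small part of the power for the primary outcome, high-frequency spectral power.

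**Working it through.** **Inputs**, all from Sample Size and Power Calculation: required number 56 (28 per group), attrition 20%, recruitment target 67, alpha 0.05, claimed power 80%.

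**1. Reproduce the plan's figure.** Adding 20% to the requirement gives 56 × 1.20 = 67.2, which rounds to 67. This is evidently how the target was obtained.

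**2. Number needed for the stated purpose.** If a fraction *a* of those recruited is lost, the number remaining is N × (1 − *a*). Setting this equal to 56 with *a* = 0.20 gives N = 56/0.80 = 70 (35 per group). The plan is 70 − 67 = 3 short.

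**3. What 67 delivers at 20% attrition.** 67 × 0.80 = 53.6, so 53 to 54 participants remain, 2 to 3 fewer than 56.

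**4. What attrition 67 can absorb.** (67 − 56)/67 = 11/67 = 16.4%, which is 20 − 16.4 = 3.6 percentage points below the stated rate.

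**5. Effect on power, accepting the plan's 80% at 56.** The section does not state sidedness; a two-sided two-sample t-test is assumed here.

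- The standardised difference that gives exactly 80% power at 28 per group is d = 0.762. The noncentrality is 0.762 × √(28 × 28/56) = 2.85 on 54 degrees of freedom.
- With 53 remaining (27 + 26), the noncentrality is 0.762 × √(27 × 26/53) = 2.77 on 51 degrees of freedom, and power is 77.7%.
- At the expected 53.6 (26.8 per group), power is 78.2%.

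The attrition step alone therefore costs about 2 points, and only if attrition reaches the full 20%. At or below 16.4% there is no shortfall.

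**The case against.** **The requirement is only approximate, and the gap is three people.** This is fair as to size and is why the point is minor. But the approximation attaches to the 56, whereas the error lies in the step from 56 to 67. For 67 to survive a 20% loss, the requirement would have to be 53 or 54, and the plan fixes 28 per group.

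**Intention-to-treat analysis with imputation keeps everyone in.** Imputation keeps participants in the data set but adds no observed outcome information, so it does not restore what dropout removes. The plan itself treats attrition as a loss, since it inflates recruitment to cover it.

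**The detail may sit in a fuller document.** Nothing is alleged to be missing. The number and the rate are both stated, and they disagree.

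**A stronger reading.** A reader might infer that power at 20% attrition drops to about 72%. The stated means and standard deviations (205.7 ± 205.7 and 568.0 ± 696.0) give a difference of 362.3, a pooled standard deviation of 513.2 and d = 0.706. A two-sided unadjusted t-test then has 73.7% power at 28 per group and 71.8% at 26.8 per group. The documents do not support charging that to the attrition error, for three reasons:

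- The fall from 80% to 73.7% is already present at 56. It belongs to the separate question of whether 56 follows from those inputs. The attrition step accounts only for 73.7% to 71.8%, again about 2 points.
- The section names neither the test nor its sidedness. With the same d, a one-sided t-test gives 83.2% at 28 per group and about 81.7% at 26.8.
- The planned analysis is covariance adjustment for baseline. The article gives no baseline-to-follow-up correlation. If it were 0.5 (an assumption), two-sided power at 26.8 per group would be about 83%.

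Writing 72% straight after a sentence claiming 80% at 56 would also create a new contradiction, because losing two or three participants cannot account for 8 points.

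**Conclusion.** The point holds as a minor arithmetic error. Steps 2 to 4 above rest only on the 56, the 67 and the 20% in the article, with attrition understood as a share of those recruited; they need no assumption about the test. The cost of about 2 points of power, from 80% to about 78%, does rest on assumptions: that the plan's 80% at 56 is right, that the test is a two-sided t-test, and that attrition reaches 20%. The error does not touch the choice of outcome, the analysis method or bias, and it does not show that the trial is seriously underpowered.

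**What to change.** Replace the attrition sentence with a statement that 67 recruits allow for about 16% attrition and that at 20% attrition about 53 to 54 participants would remain. If a power figure is wanted, give about 78%, on condition that 80% at 56 is accepted and the test is a two-sided t-test. This is one corrected sentence and needs no further participants.

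If the 20% allowance is to be kept, the consistent target is 70, at a cost of three more recruits. That target keeps 56 on average and is not a guarantee: if dropouts were independent with probability 20% each, at least 56 would remain with probability 57% when 70 are recruited, against 29% when 67 are.

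Should the 56 itself be revised, the new figure should be divided by 0.80 rather than multiplied by 1.20.

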### Participants

Eligibility criteria include: Adult (> 18 years) employed in a full-time academic or general staff office position at the University of Western Sydney; not currently engaged in regular yoga practice; available to attend three yoga sessions per week during lunch break, ability to communicate in English; no acute or chronic medical conditions which would make yoga potentially hazardous or primary outcomes impossible to assess as outlined by the *American College of Sports Medicine *(ACSM) [27]; willingness and cognitive ability to provide written informed consent. Participants will be pre-screened for participation using the *Physical Activity Readiness Questionnaire *[28], and a standardised health history questionnaire. Individuals deemed moderate-risk [27] will require the approval of their physician prior to participation. High-risk individuals [27] will be excluded.

### Randomization

Participants will be randomized *via *computer-generated randomly permuted blocks [29] stratified by gender and age (< 50 years; > 50 years) into an experimental group and no-treatment control group. An investigator not involved in testing or delivery of the intervention will prepare the randomization assignments. Group assignment will be delivered to participants in sealed envelopes upon the completion of baseline testing.

### Interventions

#### Experimental Group

Participants randomized to the experimental condition will engage in a 10-week yoga program delivered at their place of work (University of Western Sydney, Campbelltown Campus). The yoga sessions will be group-based, prescribed three times per week during lunch hour (approximately 50 minutes per session), and will be led by an experienced yoga instructor from Yoga Synergy Pty Ltd (Sydney, Australia) [10]. The program will involve teaching beginner students safely and progressively over 10 weeks a yoga sequence that incorporates *asanas *(poses and postures), *vinyasa *(exercises), *pranayama *(breathing control) and meditation. The sequence design will be aimed at developing strength, flexibility, cardiovascular fitness, and the ability to deal with stress. Many postures incorporate a simple and a more challenging version so participants will be able to choose the level of difficulty that is appropriate to them on any given day. All participants will be advised to change into appropriate clothing prior to arriving at the venue.

